### Recruitment of knowledge broker dyad

The knowledge broker dyad will consist of a pharmacist and a MAC representative. Each aged care provider organisation will employ or contract their own knowledge broker dyad(s) for each participating RACF through a local expression of interest process. Use of a local knowledge broker is intended to build on existing relationships between the knowledge broker dyad and staff within each RACF, as introducing external knowledge brokers may be less effective [33]. The knowledge broker dyad will work at the RACF-level, and individual knowledge brokers may work across more than one RACF (e.g. a pharmacist may work across two RACFs and collaborate with a different MAC representative for each RACF).

Pharmacists will be eligible to be a knowledge broker if they are:Registered with the Australian Health Practitioner Regulation Agency (AHPRA)Available to commit to 0.1 full time equivalent per RACF for the 9-month intervention (approximately 4 h per week for the knowledge broker role and 0.5 h per week for trial-related tasks [e.g. attending trial meetings, documentation]); andAble to complete specific tasks of the research project, and all relevant aged care provider organisation induction and occupation, health and safety requirements.

Prior aged care experience and credentialing to complete medication management reviews or be an aged care on-site pharmacist will be desirable but not a requirement.

MAC representatives will be eligible to be a knowledge broker if they are the MAC chair or another suitable current MAC member for their RACF’s MAC, and if they are:Registered with AHPRA (e.g. registered nurse), or have a health professional background (e.g. management staff working in a non-clinical role).Available to commit to 1.5 h per week per RACF for the 9-month intervention period (approximately 1 h per week for the knowledge broker role and 0.5 h per week for trial-related tasks [e.g. attending trial meetings, documentation]); andAble to complete specific tasks of the research project.A non-pharmacist MAC representative will be desirable but not a requirement.

A member of the Project Management Team will meet with each potential dyad member (pharmacist and MAC representative), provide the explanatory statement and an opportunity to ask questions, and obtain written informed consent.

### Recruitment of the national quality improvement collaborative (MEGA-MAC collaborative)

The MEGA-MAC collaborative will comprise the knowledge broker dyads plus a multidisciplinary panel of clinical experts, implementation scientists, and resident and caregiver representatives. The clinical experts, implementation scientists and consumers will be identified via professional contacts of the Project Management Team or participating aged care provider organisations. Potential participants will be eligible to be a MEGA-MAC collaborative panel member if they are: registered with AHPRA (e.g. medication practitioner, pharmacist, registered nurse); working in implementation science; or identify as a resident or caregiver representative. The Project Management Team will provide potential MEGA-MAC collaborative panel members with the explanatory statement and obtain written informed consent from the MEGA-MAC collaborative panel member.

### Knowledge broker dyad training

Knowledge broker training will be a requirement for pharmacists and desirable for MAC representatives and MEGA-MAC collaborative panel members. This is because the knowledge broker pharmacist will be responsible for leading the delivery of the intervention. Training will involve a series of online education modules (approximately 4 h in total) developed for the MEGA-MAC trial and hosted on the Guroo Learning platform. Content related to knowledge translation and change management will be based on previous education developed for the national quality improvement collaborative for implementing Australia’s Clinical Practice Guidelines and Principles of Care for People Living with Dementia [20]. The self-paced learning in this trial will encourage participants to reflect on their own experience, apply learnings to case studies, and discuss the education material via a chat function. The education modules will cover the following topics:Introduction into medication safety and the quality use of medications in RACFs, including introduction to the Guiding Principles and the role of MACs.Knowledge translation and the role of a knowledge broker, including a focus on the practical application of knowledge translation and how to be an effective knowledge broker dyad.Change management and local action plans, including barriers and enablers to change and guidance on how to develop local action plans.MEGA-MAC trial design and trial indicators.

## Intervention

### Knowledge broker dyad

The intervention will involve the knowledge broker dyad implementing the Guiding Principles together with the RACF and MAC, with support from the MEGA-MAC collaborative. The knowledge broker dyad will act as a knowledge manager, capacity builder, and linking agent [15], with activities including:Knowledge manager: Distributing and raising awareness about the Guiding Principles; embedding and applying the Guiding Principles into local contexts, policies and procedures; and assessing barriers and enablers to implementation in the local context.Linkage agent: Facilitating collaboration between key onsite and off-site stakeholders (e.g. aged care provider management, quality improvement teams, medical practitioners, nurses, aged care workers, allied health, and community pharmacists); engaging with other knowledge broker dyads via the MEGA-MAC collaborative; and being a conduit between the Project Management Team and the RACF employed staff and visiting team members.Capacity builder: Developing staff knowledge and skills to facilitate and enable improvements in medication management in line with the Guiding Principles; conducting audits and providing feedback on concordance with the Guiding Principles using the MEGA-MAC trial indicators to inform development of quality improvement initiatives; and evaluating effectiveness of those quality improvement initiatives.

The knowledge broker dyad will develop, implement, and evaluate RACF-specific local action plans quarterly based on each RACF's needs (Fig. 2). The local action plans will follow a systems approach using the United States Institute for Healthcare Improvement Model (IHI model) [34] and the Plan-Do-Study-Act (PDSA) cycle [35]. The knowledge broker dyad will use the three fundamental questions in the IHI model to identify why a change is needed, what improvement will look like and the changes that will result in improvement [34]. The PDSA cycle will be used as a systematic framework for continuous improvement in the real-world setting, including adapting planned actions according to ongoing feedback and monitoring [35]. The knowledge broker dyad will identify areas for improvement informed by a local context assessment, MEGA-MAC trial indicator results and with input from RACF staff, MAC members and the MEGA-MAC collaborative. Knowledge broker dyads will receive feedback on their local action plans from the Project Management Team, knowledge broker peers and the MEGA-MAC collaborative (Table 1).

**Fig. 2 Fig2:**
[figure not shown]
Description of the knowledge broker dyad intervention informed by the Institute of Health Improvement (IHI) model and the plan-do-study-act (PDSA) cycle. Abbreviations: KB, knowledge broker; MAC, medication advisory committee; RACF, residential aged care facility; SMART, specific, measurable, achievable, relevant, timely

**Table 1 Tab1:** Knowledge broker dyad study activity requirements

Time point	Reporting and study activity requirement
−1-month time point	*Training and orientation:* Knowledge broker dyad will participate in RACF training/orientation and complete MEGA-MAC study training
Baseline (0-month time point)	*Local action plan:* Knowledge broker dyad will collaboratively develop local action plans, submit their local action plans for MEGA-MAC collaborative expert and peer review, provide feedback on their peers’ local action plans and present their local action plans at local MAC meetings *Intervention:* Delivery of knowledge broker dyad services as per local action plans and attendance at local MAC and MEGA-MAC meetings *Process evaluation:* Online survey with MEGA-MAC meeting attendees at the conclusion of MEGA-MAC meeting
3-month time point	*Local action plan:* Knowledge broker dyad will collaboratively reflect and revise local action plans, submit their local action plans for MEGA-MAC collaborative expert and peer review, provide feedback on peers’ local action plans and present their local action plans at local MAC meetings *Intervention:* Ongoing delivery of knowledge broker services as per local action plans and attendance at local MAC and MEGA-MAC meetings *Process evaluation:* Semi-structured interviews with knowledge broker dyads and online survey with MEGA-MAC meeting attendees
6-month time point	*Local action plan:* Knowledge broker dyad will collaboratively reflect and revise local action plans, submit their local action plans for MEGA-MAC collaborative expert and peer review, provide feedback on peers’ local action plans and present their local action plans at local MAC meetings *Intervention:* Ongoing delivery of knowledge broker services as per local action plans and attendance at local MAC and MEGA-MAC meetings *Process evaluation:* Semi-structured interviews with knowledge broker dyads and online survey with MEGA-MAC attendees
9-month time point	*Local action plan:* Knowledge broker dyad will reflect on success and challenges for previous quarter and present their findings at the local MAC and final MEGA-MAC meeting *Process evaluation:* Semi-structured interviews with knowledge broker dyads and online survey with MEGA-MAC attendees

*RACF* residential aged care facility, *MAC* medication advisory committee, *MEGA-MAC* national quality improvement collaborative

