**Methods:**

The Maximising Embedded Pharmacists in AGed CAre Medication Advisory Committees (MEGA-MAC) trial will be conducted in partnership with RACFs operated by three aged care provider organizations across four states of Australia. The intervention will involve knowledge broker dyads (pharmacist plus a MAC representative [e.g. nurse]) developing, implementing and evaluating RACF-specific local action plans to implement the Guiding Principles in up to 15 RACFs. Knowledge broker dyads will be supported by a national quality improvement collaborative (MEGA-MAC collaborative) comprising clinical experts, implementation scientists and resident and caregiver representatives. An interrupted time series design will be used to assess change over time with three pre-intervention (-6, -3 and 0 months) and three post-intervention assessment time points (+ 3, + 6, + 9 months). The primary outcome will be change in pre/post RACF-level concordance with the Guiding Principles measured using quality indicators (score 0 to 28, higher scores = greater concordance). A net benefit analysis will be conducted to examine the relative costs and benefits of implementing the intervention.

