### Recruitment, eligibility and consent of RACFs

The three aged care provider organisations’ leadership team will identify RACFs that are eligible and interested in participating. RACFs will be eligible if they have a MAC or commit to establishing a MAC by the commencement of the trial. Once eligible RACFs are identified at the aged care provider organisational level, a member of the Project Management Team will explain the trial to eligible RACFs, provide the explanatory statement and obtain written informed consent from the RACF manager or an authorised representative of the aged care provider organisation.

This will be a RACF-level intervention, individual residents will not be recruited to participate. Nurses, aged care workers, visiting pharmacists and medical practitioners at each RACF and MAC members will be made aware of the objectives of the trial and the nature of the intervention via letters, posters and notice boards. Residents and their families will be made aware of the trial through distribution of notices and posters at each RACF.

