### Data collection

Data will be collected from the participating RACFs at six timepoints (−6, −3, baseline, 3, 6, 9 months) by trained data collectors (aged care nurses, health or care professionals employed or contracted by each of the participating aged care provider organisations) (Table 2). Data collectors will attend an online training webinar on data collection led by the Project Management Team and will have access to data collection manuals and recorded training webinars to ensure consistency of data collection. Pre-intervention data (−6, −3, 0 months) will be collected retrospectively at or before baseline. Post-intervention data (+ 3, + 6, and + 9) will be collected prospectively. Trial data will be collected using a series of standard data collection forms and managed using Research Electronic Data Capture (REDCap), an electronic data capture tool hosted and managed by Helix (Monash University). REDCap is a secure, web-based software platform designed to support data capture for research studies [36, 37]. Trial data will be stored for a minimum of 15 years after publication of result in accordance with Australian National Health and Medical Research council (NHMRC) and Monash University guidance for medical research involving clinical trials. The final dataset will only be accessible to the investigators and statistician or epidemiologist.

**Table 2 Tab2:** SPIRIT diagram – schedule of enrolment, intervention and assessment for the MEGA-MAC study

	Study period							Data source
Timepoint (months)	Pre-intervention period		Enrolment	Baseline	Intervention period			
	−6	−3	*-t*	0	3	6	9	
RACF enrolment								
Eligibility screen			x					
Consent			x					
Intervention								
KB dyad recruitment			x					
MEGA-MAC collaborative panel recruitment			x					
KB training			x					
Intervention implementation				x	x	x	x	
Data collection								
RACF characteristics information				x				Clinical and administration records; knowledge broker dyads
MAC characteristics information				x			x	Clinical and administration records; knowledge broker dyads
KB dyad and MEGA-MAC collaborative panel demographic information			x					Knowledge brokers and MEGA-MAC members

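### The month-0 assessment counts as pre-intervention although dyad orientation and indicator training are placed at -1 month, and the primary model is sensitive to any gain brought forward to month 0

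*Protocol article*

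**What the plan says.** The Data collection section states: "Pre-intervention data (−6, −3, 0 months) will be collected retrospectively at or before baseline". Month 0 is therefore the third of three pre-intervention assessments.

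Table 1 gives the -1-month activity: "Knowledge broker dyad will participate in RACF training/orientation and complete MEGA-MAC study training". The section on dyad training lists the module topics, the last of which is "MEGA-MAC trial design and trial indicators". It also says who must train: "Knowledge broker training will be a requirement for pharmacists and desirable for MAC representatives and MEGA-MAC collaborative panel members". Table 2 lists dyad training before baseline, under its Intervention rows.

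Delivery starts at baseline, where Table 1 has "Delivery of knowledge broker dyad services as per local action plans and attendance at local MAC and MEGA-MAC meetings".

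The Effectiveness analysis section specifies a linear mixed model with a binary period factor, trial month as a continuous fixed factor, and site nested in MAC as random effects. A model with a period-by-month interaction is additional. The article describes no transition period and no analysis that sets month 0 apart.

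**The concern.** By month 0 the dyad pharmacist should have learned which items are scored. If an RACF acts on that knowledge before month 0, the improvement enters the baseline.

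The domains differ in how far they could move:
- **Domain 2 (ten policy items, Table 4)** asks only whether a document is available and current. With no look-back, a policy renewed in the training month scores in full at month 0.
- **Domains 1 and 3 (Tables 3 and 5)** refer to the last quarter or to admissions in the last 3 months. If orientation falls at -1 month, one month of three is exposed.
- **Domain 4 (Table 6)** has three indicators with a 12-month look-back, which can move little. The fourth concerns residents admitted in the last 3 months.

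Month 0 also carries much weight in the primary model. An early gain there lowers the pre/post contrast and at the same time looks like an existing upward trend, which the common month slope projects into the post-intervention period. The stake is a missed or understated benefit.

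**Working it through.** The plan gives no figure for this point. Its 86% power statement is not in dispute here.

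**Inputs.** Times -6, -3, 0 (pre) and 3, 6, 9 (post); primary model score = a + b·post + c·month. I take the random effects to be intercepts and the data to be complete and balanced. The generalised least-squares weights for b then equal the ordinary least-squares weights, checked at intraclass correlations of 0.25, 0.5 and 0.8.

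**Step 1: weights for b.** Regress the period indicator on month.
- Mean month = 1.5; sum of squares of month = 2 × (7.5² + 4.5² + 1.5²) = 157.5.
- Cross-product with period = 13.5; slope = 13.5/157.5 = 0.0857.
- Residual sum of squares of period = 1.5 - 13.5²/157.5 = 0.3429.
- Weight at month 0 = (-0.5 + 1.5 × 0.0857)/0.3429 = -1.083.

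| Month | -6 | -3 | 0 | 3 | 6 | 9 |
|---|---|---|---|---|---|---|
| Weight | +0.417 | -0.333 | -1.083 | +1.083 | +0.333 | -0.417 |

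**Step 2: gain e brought forward, scores at +3, +6 and +9 unchanged.** The pre mean rises by e/3. The fitted slope rises by e/12 per month, and the pre and post means lie 9 months apart (-3 to 6). Change in b = -e/3 - 9e/12 = -13e/12 = -1.083e. A plain pre/post mean difference would lose only 0.333e.

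| Assumed average early gain (points of 28) | Loss in period coefficient | Loss in plain mean difference |
|---|---|---|
| 0.25 | 0.27 | 0.08 |
| 0.5 | 0.54 | 0.17 |
| 1 | 1.08 | 0.33 |

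The protocol gives no size for an early gain, so the first column is an assumed range.

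**Step 3: additional gain e that starts at month 0 and persists.** Net weight = -1.083 + 1.083 + 0.333 - 0.417 = -0.083. The period coefficient shows -0.083e instead of e, and the fitted slope takes up the gain.

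**Step 4: dependence on the model.** In the additional interaction model, with the step read at month 0, the month-0 weight is -0.833. With the correlations from the sample-size section (0.5 pre, 0.25 post) and an assumed pre-post correlation of 0.375, generalised least squares gives -1.233.

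**Step 5: precision of the alternatives.** The variance of b, in residual variances per site, is the reciprocal of the residual sum of squares in Step 1.
- All six points: 1/0.3429 = 2.917.
- Month 0 excluded: 1.2 - 12.6²/154.8 = 0.1744, so 5.733. Ratio 1.97; standard error × 1.40.
- Last pre point moved to -1: 1.5 - 14²/161.33 = 0.2851, so 3.507. Ratio 1.20; standard error × 1.10. The moved point still has weight -1.043.

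**The case against.** The case for leaving the plan alone is substantial.

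- Nothing in the protocol shows that scores rise before month 0. Local action plans, their presentation to the MAC and delivery of services all begin at baseline. What precedes is orientation and about 4 hours of self-paced online modules, mandatory only for the pharmacist. This stands, and it makes the loss conditional.
- A reader might infer that the dyad is already working on site from -1 month. Table 1 mentions RACF training/orientation and does not say where it takes place.
- A reader might cite the notices, by which staff "will be made aware of the objectives of the trial and the nature of the intervention via letters, posters and notice boards", as exposure before month 0. No date is given for them, so they do not show it.
- A reader might conclude that the model subtracts every early gain more than one-for-one. That holds only for gains brought forward with later scores unchanged. For an added gain that persists, the coefficient hardly moves, and the fault is that the gain is not credited.
- The "will be collected retrospectively at or before baseline" wording, with data collection manuals that are not shown, may settle the month-0 reference date in practice. The article's wording says when data are gathered and does not place the reference date before orientation.
- Moving the last pre-intervention point to -1 month is tempting because the records are retrospective. Its 3-month look-back would run from -4 to -1 and overlap the -3 assessment's window (-6 to -3). Two Domain 4 indicators also follow the national quality indicator (NQIP) audit. This objection stands, and that change is not recommended.

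**Conclusion.** The point holds as a conditional weakness. An assessment that follows orientation and indicator training is coded as fully pre-intervention, and the primary model gives it a weight of -1.083. The loss is 1.08 points of the period coefficient per point brought forward, or about 0.27 to 1.08 points for assumed average early gains of 0.25 to 1 point. If no early gain occurs, there is no loss.

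The result rests on three assumptions: random intercepts, complete data at all six times, and orientation actually falling about a month before the month-0 reference date. The main exposure is the ten Domain 2 items.

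Any bias runs towards no effect. A reader might infer that the trial could falsely claim benefit through this route, or that its baseline is known to be contaminated; the protocol supports neither.

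**What to change.** 1. Record, for each RACF, the date orientation starts and the reference date of the month-0 assessment.
2. Take the Domain 2 month-0 status from records as at the day before orientation. Pre-intervention data are retrospective and Domain 2 has no look-back, so this needs dated policy records but no extra visit.
3. Pre-state a sensitivity analysis of the primary model that treats month 0 as a transition point and excludes it. Report it beside the primary result.
4. Keep -6, -3 and 0 as the schedule for the primary analysis.

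The cost is some added wording and two dates per RACF. The sensitivity analysis leaves two pre-intervention points and a standard error about 1.40 times larger, so it should be read for the direction and size of the shift in the estimate. It should not serve as a second test.

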### MEGA-MAC collaborative

Knowledge broker dyads will be supported by the MEGA-MAC collaborative. This will be modelled on the national quality improvement collaborative for implementing Australia’s Clinical Practice Guidelines and Principles of Care for People Living with Dementia [20]. The MEGA-MAC collaborative will act as a real-time clinical network to enable sharing of experience and expertise between the knowledge broker dyads and support the knowledge broker dyads, RACFs, MACs and aged care provider organisations to implement the Guiding Principles and ensure quality use of medications.

The MEGA-MAC collaborative will support the knowledge broker dyads through the following activities (Fig. 3):quarterly virtual ‘MEGA-MAC’ meetings (baseline, 3, 6 and 9 months);quarterly ‘MEGA-MAC’ newsletters (baseline, 3, and 6 months) that include trial updates and sharing of learnings;providing aggregate Guiding Principles concordance results from all participating RACFs that each knowledge broker dyad can use to benchmark against their RACF-level concordance;expert and peer review feedback on the knowledge broker dyads’ local action plans (baseline, 3 months and at 6 months); andongoing ad-hoc expert and peer support via virtual meetings, and informal real-time peer support via SLACK (Searchable Log of All Communication and Knowledge) chat group.

